#### Data collection procedures

After initial recruitment, all participants will have their medical records reviewed to reconfirm their eligibility. On arrival of the cholesterol blood results, CVD risk scores will be calculated by the research team, as per JBS2 guidelines[1]. In the FHQ group, familial CHD risk will also be calculated and incorporated into the overall score. Two weeks after the original consultation both clinicians and participants will be sent a letter informing them about the participant's risk status. Participants identified at average or moderate CVD risk in both groups will be sent a letter confirming status together with a leaflet on lifestyle advice. In addition to a leaflet, those at higher risk in both groups will be informed that they are at higher than average CVD risk and invited for a consultation in the practice within the next 2 weeks.

In the consultation with doctor or nurse, participants will have their CVD risk explained and given lifestyle advice and, when clinically indicated, statins will be offered, as per usual practice. Participants in the FHQ group will also have the impact of premature CHD family history on the CVD risk score explained.

At two weeks and six months after the second consultation (for high risk participants) or letter being sent (for average or moderate risk participants) all participants will be posted a set of questionnaires. Participants, who have been identified at high risk, will be invited for a qualitative interview by phone, following a purposeful, maximum variation sampling strategy in terms of being in intervention or control arm, gender, age, occupational class, ethnicity, region and having or not having a family history of premature CHD. Recruitment will continue until thematic saturation is reached. Participants in the qualitative study will be interviewed by an experienced researcher in their homes (or if the participants so desire by phone) at 2 weeks and 6 months after the consultation in the practice.

Six practices in the intervention arm will be invited to participate in a focus group to capture the practitioners' views on using family history assessment and incorporate this into their clinical decision making.

After nine months the recruited participants' computer GP records will be reviewed for prescribing of: lipid lowering, anti-obesity, and anti-thrombolytic drugs, as well as nicotine replacement therapy.

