#### Outcome measures

The primary outcome measure is the proportion of participants falling in the high risk of CVD category

The secondary outcome measures are:

i) Self-reported lifestyle changes; including changes in smoking habits, levels of exercise and fat intake[29,30]

ii): Anxiety, using the 6 item Spielberger State-Trait Anxiety Inventory (STAI)[31] and fatalism and causal attributions of heart disease using the Illness Perception Questionnaire[32,33]

iii): Perception of health-related quality of life (SF-6D, derived from SF-36, and global question 2)[34,35].

The first two groups of these measures have been used in the assessment of CHD prevention in UK primary care. Perception of health and 6 item STAI measures have been used in other studies on family history and genetic screening in primary care[21,36,37].

Qualitative interviews will be used to analyse the contextual processes that mediate lifestyle change and risk perceptions of participants identified as at high risk in both the control and the FHQ group of the study. Participants' changes in views and their perceptions of heart disease, family history, their personal risk, lifestyle, medications, ethical concerns and their social, cultural and familial context will be collected.

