#### Attrition rate

One thousand four hundred patients will be invited to participate. It is estimated that one thousand participants will complete consent and baseline questionnaire, with eight hundred completing the CVD risk assessment by having the serum cholesterol test, resulting in 400 participants recruited in each arm of the study.

Further, related to secondary outcome measures, it is estimated that 60% of recruited participants will complete the 6 month questionnaire. Hence 300 participants in each arm are expected to complete the study.

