#### Data analysis

Quantitative data: Analysis will be undertaken on an intention to treat basis in that participants will be analysed in the groups to which they were allocated. The primary time point of interest is 6 months. Practices will be included in the analysis provided complete data (the outcome of interest at baseline and at 6 months follow up, and participant/practice level data that will be adjusted for in the analysis) are available for at least one of the participants recruited to the practice. Participants within the practice with incomplete data will be excluded from the analysis. If data for the secondary outcomes are missing for the 6 month assessment, a sensitivity analysis will be performed in which data from the two week assessment will be carried forward. An analysis assuming the worst case scenario of the 6 month assessment value being the same as the baseline value will also be performed.

The distribution of participants in average, moderate and high risk categories will be described by treatment group. The increase in the proportion of participants at high risk of CVD in the next 10 years as a result of incorporating systematically collected family history into CVD risk assessment score will be presented. For the primary outcome measure and the secondary outcome measures that are binary variables, the statistical significance of the difference in the event rates (e.g. the mean proportion of participants at high risk) between the FHQ and control groups will be calculated using a weighted paired t-test after the adjustment for the pairing of practices, participant and practice level variables that are associated with the outcome of interest. A weighted paired t-test will be used because it is anticipated that there will be wide variation in the number of participants recruited per practice. The robustness of the t-test will be assessed using a permutation test. Continuous outcome variables will be analysed using a similar method with differences in the mean response between the FHQ and control groups being compared using a weighted paired t-test. 95% confidence intervals will be presented for the intervention effect for all outcome measures.

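### The 6-month time point and the baseline-plus-6-month completeness rule cannot be applied to the primary outcome, which is determined once, when the cholesterol result arrives

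*Protocol article*

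**What the plan says.** All references are to Phase 2 of the protocol article.

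- **Outcome measures:** "The primary outcome measure is the proportion of participants falling in the high risk of CVD category".
- **Data collection procedures:** "On arrival of the cholesterol blood results, CVD risk scores will be calculated by the research team, as per JBS2 guidelines". The result is then reported: "Two weeks after the original consultation both clinicians and participants will be sent a letter informing them about the participant's risk status". Follow-up at two weeks and six months is by postal questionnaire. The nine-month record review covers prescribing. No second cholesterol test or risk score is scheduled.
- **Data analysis:** "The primary time point of interest is 6 months". Practices are included "provided complete data (the outcome of interest at baseline and at 6 months follow up", plus adjustment variables) for at least one participant. "Participants within the practice with incomplete data will be excluded from the analysis". The section then analyses the primary outcome with a weighted paired t-test and makes no exception for it. Only the sensitivity analyses for missing 6-month values are introduced with reference to secondary outcomes.
- **Sample size:** 369 per group completing CVD risk assessment.
- **Attrition rate:** 400 per arm are expected to have the risk assessment. For the secondary outcomes, "it is estimated that 60% of recruited participants will complete the 6 month questionnaire", given as 300 per arm.

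**The concern.** The Data analysis rule requires a 6-month value of whichever outcome is being analysed. For the primary outcome no such value will exist. The rule therefore cannot be carried out for the comparison on which the trial was sized, and it disagrees with the Sample size and Attrition rate sections, which count everyone who completes the risk assessment.

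The article does not say how the analyst should resolve this. One resolution ignores the 6-month condition for the primary outcome and keeps everyone scored. Another treats a returned 6-month questionnaire as satisfying it. The second would discard people whose primary outcome is already known and would select the analysis set by response. Participants and practices are not blinded, and high-risk participants are invited to a consultation while the others receive a letter. Response could therefore differ by arm or by risk category. The documents give no basis for the direction or size of any resulting bias. The choice should be fixed in the text before data are seen.

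**Working it through.** **1. Is there any 6-month value of the primary outcome?**

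| Contact | What is collected | Gives a CVD risk category? |
|---|---|---|
| Recruitment and cholesterol result | Risk factors, cholesterol, family history in the FHQ arm | Yes |
| 2 weeks | Postal questionnaires | No |
| 6 months | Postal questionnaires | No |
| 9 months | Prescribing from GP records | No |

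The Phase 3 Methods section remarks that the six-month period may be long enough to detect the change in numbers identified, but it schedules no second score. Applied literally, the completeness rule leaves 0 participants in the primary analysis.

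**2. Reproducing the article's sample size.** Inputs from Sample size: 0% versus 3%, power 80%, two-sided alpha 0.05, ICC 0.01, cluster size 40.

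- The article does not name its test. For Fisher's exact test with no control events, two-sided p falls to 0.05 or below at 6 events (p = 0.030; 5 events give p = 0.061). Power is P(Bin(n, 0.03) ≥ 6). It first reaches 0.80 at n = 263 and is 0.808 at n = 265, so 265 reproduces to within 2.
- Design effect = 1 + (40 − 1) × 0.01 = 1.39. Then 265 × 1.39 = 368.35, rounded up to 369, as stated.

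**3. Size of the set if questionnaire return were used instead.** This is a supposition, not the article's rule.

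- The article states 300 per arm.
- 60% of 400 = 240 per arm.
- The two differ because 300 is 60% of 500 (half of the 1,000 expected to consent) or 75% of 400. The base of the 60% is not clear, so both are carried forward.
- Both fall short of 369.

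**4. Illustrative power.** Effective n = N / [1 + (m − 1) × 0.01], rounded down. The cluster size m is either the planned 40 or N divided by the 12 practices per arm.

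| N per arm | m | Design effect | Effective n | Fisher power |
|---|---|---|---|---|
| 400 | 40 | 1.39 | 287 | 0.86 |
| 400 | 33.3 | 1.323 | 302 | 0.89 |
| 300 | 40 | 1.39 | 215 | 0.63 |
| 300 | 25 | 1.24 | 241 | 0.73 |
| 240 | 40 | 1.39 | 172 | 0.41 |
| 240 | 20 | 1.19 | 201 | 0.56 |

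By the normal approximation the ranges are 0.84 to 0.86 at 400, 0.73 to 0.78 at 300 and 0.63 to 0.70 at 240. The ordering is the same and the loss is smaller.

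**The case against.** The strongest reply is that the authors plainly meant the 6-month condition for the questionnaire outcomes. Sample size counts those completing the risk assessment, Attrition rate ties the 60% to the secondary outcomes, and the sensitivity analyses for missing data are introduced for secondary outcomes. The literal reading leaves nobody, so it would be noticed at once and would not silently bias anything. This is probably right about intent. It does not repair the text, because Data analysis states the time point and the completeness rule without restriction and then analyses the primary outcome in the same section.

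Three further points stand and limit the finding.

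- A reader might infer that the primary result will rest on the 60% who respond. The documents do not support that. The rule asks for the outcome itself at 6 months, and a returned questionnaire does not supply a risk category.
- A reader might infer a conflict with the claimed intention-to-treat analysis. The article uses that term only to mean analysis by allocated group, and dropping incomplete cases does not contradict that definition.
- Fisher's test on a reduced sample is not the planned weighted paired t-test on matched practices, and the article says the gain from matching was not counted. The power figures are indicative only.

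**Conclusion.** The rule is wrong as written for the primary outcome. It demands a 6-month measurement that the trial does not make, and it contradicts the sections that size the primary analysis. This conclusion rests on the text alone and needs no power calculation.

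The loss of numbers is conditional. If the rule were met by questionnaire return, the primary set would be 240 to 300 per arm against 369 required. Fisher power would be about 0.41 to 0.73 across that range, against 0.86 to 0.89 with all 400. These figures assume the article's own 0% versus 3%, ICC 0.01 and cluster sizes between 20 and 40. Selection by response is possible under that reading, in an unknown direction.

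**What to change.** Reconcile Data analysis with Data collection procedures, Sample size and Attrition rate by stating three things:

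1. The primary outcome is assessed when the CVD risk score is calculated.
2. Its analysis set is every participant with a calculated CVD risk score, analysed in the allocated arm, with no 6-month data requirement.
3. The 6-month time point and the baseline-plus-6-month completeness rule apply only to the questionnaire (secondary) outcomes.

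The cost is a few sentences in the protocol, carried into the analysis plan. No new data are needed, and the expected 400 per arm stay in the primary analysis, above the 369 required. The change settles timing and analysis set only. It does not touch the separate requirement for complete adjustment variables, and it does not say which two values form the change that Sample size refers to. It also still leaves out the roughly 200 of 1,000 consenting participants expected not to complete the risk assessment, as the sample size already does.

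### The main analysis of the secondary outcomes is complete-case at 60% expected response and uses the 2-week scores only by carrying them forward, so arm differences can be biased if drop-out works differently by arm

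*Protocol article*

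**What the plan says.** The Data analysis section of Phase 2 opens with: "Analysis will be undertaken on an intention to treat basis in that participants will be analysed in the groups to which they were allocated". It names 6 months as the main time point. A practice enters the analysis if at least one of its participants has complete data, which means "the outcome of interest at baseline and at 6 months follow up, and participant/practice level data that will be adjusted for in the analysis". Then: "Participants within the practice with incomplete data will be excluded from the analysis".

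If 6-month secondary data are missing, two further analyses are planned. One carries the 2-week value forward. The other sets the 6-month value to baseline and is labelled a worst case.

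Under Data collection procedures, questionnaires are posted to all participants at 2 weeks and at 6 months. Under Attrition rate, "it is estimated that 60% of recruited participants will complete the 6 month questionnaire". The Phase 3 Methods use the 2-week SF-6D score when the 6-month score is missing, again only as a sensitivity analysis.

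**The concern.** The secondary outcomes include anxiety, fatalism, smoking, exercise, fat intake and SF-6D. Anxiety is the trial's main quantitative measure of possible psychological harm. If four in ten participants leave the main analysis, the arm comparison describes those who replied.

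Differential drop-out is possible in this design. Participants know their allocation. The family history questionnaire is expected to move more people into the high-risk category, and high-risk people are invited to a consultation while others receive only a letter. The Ethical considerations section accepts that completing the questionnaire may raise anxiety for a time. If people who were worse at 2 weeks reply less often at 6 months, and this is more marked in the FHQ arm, a complete-case comparison understates a harmful effect. The same mechanism could distort the lifestyle and SF-6D results.

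The 2-week questionnaire measures the state from which such drop-out would start, and the main analysis leaves it out. The covariate rule also removes a person whose outcome is known if one adjustment variable is missing.

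**Working it through.** **Size of the loss.** Inputs from Attrition rate: 60% completion, "resulting in 400 participants recruited in each arm of the study", 1000 with consent and baseline questionnaire (500 per arm), and "Hence 300 participants in each arm are expected to complete the study".
- 0.60 × 400 = 240, which does not reproduce 300.
- 0.60 × 500 = 300, which does.
- The loss is 40% on either base: 160 of 400 or 200 of 500. Setting 300 against 400 gives 25%, which contradicts the stated 60%.

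**General size of the bias.** The bias in the arm difference equals the missing fraction times the arm difference in the gap between missing and observed means. For an assumed gap difference of 0.1 to 0.5 SD, 0.40 × 0.1 = 0.04 SD and 0.40 × 0.5 = 0.20 SD. At 25% missing the range is 0.03 to 0.13 SD.

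**Simulation.** All inputs except the 60% response are assumptions. In SD units: 2-week score = 0.5 × baseline + noise + 0.2 × arm; 6-month score = 0.3 × baseline + 0.5 × 2-week score + noise. The true 6-month difference is 0.5 × 0.2 = 0.10. Response at 6 months is logistic in the 2-week score, 60% overall. Slopes are the fall in log-odds of response per SD, control/FHQ. The complete-case analysis is adjusted for baseline.

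| Slopes | Complete case | Using 2-week score (all answer at 2 weeks) |
|---|---|---|
| 0/0 | 0.10 | 0.10 |
| 0.3/0.3 or 0.5/0.5 | 0.10 | 0.10 |
| 0.2/0.3 | about 0.08 | 0.10 |
| 0.3/0.5 | 0.07 to 0.08 | 0.10 |
| 0.2/0.6 | about 0.05 | 0.10 |
| 0/0.5 | about 0.03 | 0.10 |

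If only 75% answer at 2 weeks, the analysis using that score gives about 0.08 in the last two rows.

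**The planned sensitivity analyses.** With purely random drop-out, the same model gives by arithmetic:
- 2-week value carried forward: 0.60 × 0.10 + 0.40 × 0.20 = 0.14.
- Baseline carried forward: 0.60 × 0.10 + 0.40 × 0 = 0.06.

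Both miss 0.10 without any selective drop-out, because each freezes a score that changes over time. With slopes 0/0.5 and 0.2/0.6 the simulation gives 0.17 to 0.18 and 0.04 to 0.05.

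**Scale.** The detectable difference at 80% power is (1.96 + 0.84) × √(2 × design effect / n), with the protocol's ICC of 0.01 and 12 practices per arm.
- n = 240: 20 per practice, design effect 1 + 19 × 0.01 = 1.19, giving 0.28 SD.
- n = 300: 25 per practice, design effect 1.24, giving 0.25 SD.

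**The case against.** Much of the case for leaving the plan alone is sound.

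- A reader might infer that complete case fails whenever drop-out is related to the 2-week score. It does not: with equal slopes the arm difference is essentially unbiased. Bias needs dependence that differs by arm, and the documents give no evidence on that. The slopes are assumptions, and the mildest contrast moves 0.10 only to about 0.08.
- A reader might infer that the intention-to-treat label is false. The protocol defines it as analysis by allocated group and discloses the exclusion in the same paragraph. Nobody is moved between arms. What stands is that the analysed set is responders and should be described so.
- A reader might infer that the 2-week data are ignored. They are used in two sensitivity analyses, and a missing 2-week form alone excludes nobody.
- The anxiety mechanism is only possible. The family history questionnaire is completed with the baseline pack, the rise in anxiety is called transient, and nothing says that it persists or drives non-response.
- The covariate rule has no calculable cost here: the number of covariates and their missingness are not given, and several are likely to be known for everyone.
- The trial is exploratory, these are secondary outcomes, and a bias of 0.05 to 0.07 SD is small beside a detectable difference of 0.25 to 0.28 SD.

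These points limit the size of the problem. They do not remove it, because the exclusion rule is stated and not left open, and the fallback analyses have errors of their own.

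**Conclusion.** The point holds as a weakness in a stated analysis rule and should be changed. By the protocol's own 60%, about 40% of participants are left out of the main analysis of every secondary outcome that rests on the 6-month questionnaire. The arm difference can then be biased if response depends on the earlier score differently by arm. Under the assumed slopes 0/0.5 and 0.2/0.6, a true 0.10 SD appears as about 0.03 to 0.05. With equal slopes, or random drop-out, there is no material bias. Using the 2-week score recovers about 0.08 to 0.10, depending on 2-week response, which the protocol does not state.

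The documents do not show that bias will occur, nor that harm will be hidden. The point does not extend to the primary outcome: the risk category is calculated soon after recruitment and does not depend on the 6-month questionnaire.

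**What to change.** For each secondary outcome, make the main analysis a likelihood-based repeated-measures analysis of the baseline, 2-week and 6-month data, or multiple imputation by arm from the same data. Either must allow for clustering within practices. Carry the adjusted practice means into the planned weighted paired t-test. Impute missing baseline covariates instead of excluding the person.

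Keep complete case as a sensitivity analysis and describe it as responders analysed by allocated group. If the carry-forward analyses are kept, do not treat them as bounds, and drop the worst-case label from the baseline version. In Attrition rate, state whether the 60% applies to 400 or 500 per arm and correct the 300 if it is 400.

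The cost is analysis wording, some programming and reliance on a missing-at-random assumption, which is only partly met if many 2-week forms are missing too. No new data are needed.

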Primary prevention of CHD through lifestyle advice has sometimes yielded modest results[11] although, for example, behavioural interventions targeted at "at risk" patients have produced encouraging findings[12]. There is evidence that interventions that have targeted the family as a whole, rather than individuals, are more effective[13], and it has been reported that young individuals who were aware of their family history of CHD were less likely to smoke[14]. This evidence suggests that a family history approach, targeted at "at risk" individuals and those requesting CHD assessment, could motivate lifestyle change. However, it has been suggested that assessment of inherited risk may produce fatalism or anxiety[15], although these findings have not been corroborated in other studies[16]. Furthermore, people from different backgrounds have different understanding of the causes of heart disease; research has also discovered varied "lay models" of the risk associated with a family history of heart disease [17-19]. In light of these findings, it has been emphasized that to be effective, CHD prevention needs in-depth sensitivity to the ethnically and socioeconomically diverse patients' personal and cultural models of disease and family history [17,20]. Still, patients' interpretations of, and reactions to, incorporating family history into CHD risk assessment have not been studied. We have previously explored the psychological impact of a general family history questionnaire (FHQ)[21] and the validation of this instrument [22]. We have completed a qualitative pilot study on the feasibility of incorporating family history into CHD assessment from a risk communication point of view [23]. However, in order to inform policy the assessment of the clinical utility of using family history is now needed as a priority, alongside work such as that by the CDC Family HealthWare project, and prior to the development *de novo *of further tools[6]. This should include examination of the behavioural and psychological effects of CHD interventions using family history assessment. Moreover a better understanding of the implications of being identified as at higher risk of heart disease (due to a family history of premature CHD), for individuals from different social and ethnic backgrounds is also needed.

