### Methods

A cost analysis will be undertaken. Resource items likely to change as a result of the intervention (as well as the cost of developing and providing the intervention) will be identified and measured (collected using MIQUEST software) during phase 1 and 2. Unit costs will be derived from national published data[40,41] and used to value the resources measured for a common price year.

If the family history tool is to improve outcomes it not only needs to identify more at-risk individuals at an earlier stage (although this is likely to induce some benefit compared to usual practice in and of itself) but also lead to behavioural change. Such behavioural change is likely to take time as people go through stages of change towards permanent change. Therefore, the six month period of the trial may only be sufficient to detect the change in numbers identified rather than any actual change to health-related quality of life brought about through behavioural change. To test if this is in fact the case, two outcomes will be measured and two approaches to economic evaluation employed. This study will estimate the cost-effectiveness in terms of cost per additional high risk individual identified and the cost utility using the SF-6D administered at baseline and 6 months[35] to estimate the cost per QALY over the trial period (with use of 2 week score for sensitivity analysis, if 6 month score not available). Both analyses enable technical efficiency questions to be addressed, that is how best to identify those at high risk of CHD (applying a systematic approach to family history collection or not) whilst the cost-utility analysis will also enable allocative efficiency questions to be addressed, that is whether resources spent on using a systematic approach to CHD family history collection are considered cost-effective compared to a diverse range of other health interventions or services.

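### Setting missing 6-month values to baseline is labelled the worst case, but it is not one for anxiety and fatalism, where the effect of concern is a rise

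*Protocol article*

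**What the plan says.** The Data analysis section of Phase 2 fixes the time point: "The primary time point of interest is 6 months". The main analysis uses complete cases: "Participants within the practice with incomplete data will be excluded from the analysis". Two sensitivity analyses deal with secondary outcomes missing at 6 months. In the first, "data from the two week assessment will be carried forward". The second is described as follows: "An analysis assuming the worst case scenario of the 6 month assessment value being the same as the baseline value". Neither rule is split by type of outcome.

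The Outcome measures section lists three groups of secondary outcomes: lifestyle (smoking, exercise, fat intake); anxiety on the six-item STAI, with fatalism and causal attributions; and health-related quality of life. The Background gives the direction of concern for the second group, reporting a suggestion that "assessment of inherited risk may produce fatalism or anxiety", and adds that other studies have not confirmed it. Outcome (3) makes anxiety and fatalism part of the comparison between arms.

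Two remarks bear on timing. Ethical considerations says that completing the FHQ could raise anxiety for a short while. Phase 3, Methods, says of behaviour: "Such behavioural change is likely to take time".

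**The concern.** A worst-case analysis should show whether a conclusion survives when the missing data go against it. For lifestyle outcomes the hoped-for result is change, so assuming none in non-responders is pessimistic and the label fits. For anxiety and fatalism the conclusion to be stressed is that family history assessment does no psychological harm. Here, giving every non-responder a change of zero removes any harm among them by assumption.

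The scenario that matters is one in which people distressed by their result stop returning questionnaires. With a quarter to two fifths of 6-month values expected to be missing, a reader who sees that the absence of harm held in the worst case would be falsely reassured.

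**Working it through.** **Share missing.** The Attrition rate section expects 1,000 people to consent and complete baseline, and 800 (400 per arm) to complete risk assessment. It then expects 60% of those recruited, stated as 300 per arm, to complete 6 months.
- 0.60 × 1,000 / 2 = 300 per arm, which reproduces the stated figure on the 1,000 base.
- 0.60 × 400 = 240 per arm, which does not.
- 300 / 400 = 0.75.

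The completion share f is therefore taken as 0.60 to 0.75, so 25% to 40% are missing.

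**Formulas.** Let d_c be the between-arm difference in mean change among completers and d_m the same difference among non-responders, with similar completion in both arms and across practices.
- Full difference = f × d_c + (1 − f) × d_m
- Baseline substituted = f × d_c + (1 − f) × 0 = f × d_c

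The second line does not contain d_m. Whatever happened to non-responders, the result is the completers' difference multiplied by 0.60 to 0.75.

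**Illustrations for anxiety or fatalism.** The protocol gives no SD or effect size for these outcomes, so the values below are assumptions, in SD units, with positive meaning worse in the FHQ arm.

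| d_c | d_m | Full difference, f = 0.60 / 0.75 | Baseline substituted, f = 0.60 / 0.75 |
|---|---|---|---|
| 0.20 | 0.20 | 0.20 / 0.20 | 0.12 / 0.15 |
| 0.20 | 0.40 | 0.28 / 0.25 | 0.12 / 0.15 |
| 0 | 0.40 | 0.16 / 0.10 | 0 / 0 |

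In the last row the harm lies wholly among non-responders. Complete cases give 0, and so does the analysis labelled worst case.

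**Two-week values carried forward.** Supposing that all 6-month non-responders had replied at 2 weeks, the estimate is f × d(6 months) + (1 − f) × d(2 weeks).
- Anxiety difference 0.30 at 2 weeks, gone by 6 months: 0.40 × 0.30 = 0.12, or 0.25 × 0.30 = 0.075, where the 6-month difference is 0.
- Behaviour difference 0 at 2 weeks and 0.30 at 6 months: 0.60 × 0.30 = 0.18, or 0.75 × 0.30 = 0.225, where the 6-month difference is 0.30.
- Third row of the table, with the distress arising only after 2 weeks: the carried-forward difference is 0, so the estimate is again 0.

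This analysis can therefore be adverse for anxiety, but only through distress already recorded at 2 weeks. It cannot help those with no 2-week reply.

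**Limit of the 0.60 to 0.75 factor.** If completion differs by arm, each arm's mean change is multiplied by its own share. For example, with an assumed fall of 0.30 SD in both arms, no effect, and completion of 70% (FHQ) and 50% (control), baseline substitution gives 0.70 × (−0.30) − 0.50 × (−0.30) = −0.06, a small spurious benefit.

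**The case against.** The label fits the lifestyle outcomes, which are listed first, and a single sentence in a condensed article may have been written with those in mind. The outcomes are secondary, the study is exploratory, and fuller sensitivity models may sit in an analysis plan that is not shown. All of this stands and limits the weight of the point. It does not remove it, because the article itself states the rule and its label for all secondary outcomes.

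Three stronger readings are tempting, and the document does not support them.

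- *Baseline substitution favours the intervention on harm.* That follows only if non-responders' scores would have risen. FHQ-arm participants receive the FHQ in the same pack as the baseline measures (Recruitment), so a short-lived rise could already be in that arm's baseline and be carried forward. Anxiety could also fall below baseline by 6 months, which would make the substitution pessimistic. What stands is that it is not a worst case.
- *Carrying 2-week values forward contradicts the protocol's account of timing.* The remark on transient anxiety concerns filling in the form, whereas the 2-week questionnaire is timed from the later letter or consultation. The remark on behaviour is worded as a likelihood. A sensitivity analysis may also make an assumption its authors think improbable. There is a tension, since a constant effect from 2 weeks to 6 months is assumed, but no contradiction.
- *Neither sensitivity analysis probes harm.* If distress is highest early, the 2-week analysis is the adverse one for anxiety. The uncovered gap is distress arising after 2 weeks and people who did not reply then.

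**Conclusion.** The point holds for anxiety and fatalism. Where the effect of concern is a rise, zero rise in every non-responder cannot be the worst case. The stated analysis is insensitive to what happened to non-responders and shrinks the completers' difference in change by 25% to 40%. That size rests on the protocol's own completion figures and on similar completion in the two arms; the SD-unit examples are illustrations only. The label is reasonable for smoking, exercise and fat intake. The primary outcome and the sample size are untouched, because the substitution rules apply only to secondary outcomes.

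**What to change.** 1. Rename the baseline-carried analysis 'no change', and present it as the pessimistic case for lifestyle outcomes only.
2. For STAI and fatalism, add a delta-shift analysis in which FHQ-arm non-responders score worse than completers. Increase the shift until the conclusion changes, and report the shift at which it does. Each 0.10 SD of shift moves the between-arm estimate by 0.10 × 0.25 = 0.025 to 0.10 × 0.40 = 0.04 SD.
3. The shift may be built on multiple imputation using baseline and 2-week data and allowing for practice and pair. The existing analyses need not be replaced. The 2-week analysis can stay, with its constant-effect assumption stated.

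The cost is a change of wording and modest extra programming. No new data are needed.
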